## Study procedures on each study day

The subject recruitment will start in February 2018 according to the inclusion and exclusion criteria and will be conducted at the Pain Outpatient Department (Schmerzambulanz) of the MHH.

At visit 1 (screening), written informed consent will be obtained. Subjects will undergo a physical examination and medical history taking. In- and exclusion criteria will be checked. Subjects will be familiarized with the floating tank. After this, the primary and secondary long-term outcomes will be assessed, as well as the expectancy/credibility rating.

At visits 2 - 6 (intervention), each separated by  $4 \pm 2$  days, in- and exclusion criteria will be checked again. Secondary short-term outcomes 1, 2 and 3 will be assessed. After this, a 5-minute ECG will be recorded for HRV analysis (short-term outcome 4). Subjects will then put on their bathing suits, take a shower and insert ear plugs before entering the floating tank (Tranquility, Floataway, Hingham, GB). The float itself will take 90 minutes. After the floating session subjects will leave the tank and take a shower to remove excess saline. Another 5-minute ECG will be recorded for HRV analysis (short-term outcome 4), before short-term outcomes 5 and 6 will be assessed.

After the last intervention, the subject is provided with a sealed envelope containing the questionnaires for the assessment of primary and secondary long-term outcomes and discharged.

On day 7 after visit no. 6 the subject is called by telephone and asked to fill out all questionnaires in the envelope and return it by mail.

This will be repeated at 12 weeks and 24 weeks after visit no. 6. Subjects in the intervention and control group will be unblinded after receipt of the last questionnaires.

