## Data analysis

All statistical analyses will be conducted using R (<https://www.r-project.org/>) and Python (<https://www.python.org/>). Pain and sensation drawings will be analysed with the FMRIB Software Library (<https://fsl.fmrib.ox.ac.uk/fsl/>).

The statistical test for the primary outcome will be a two-tailed two-sample t-test of the differences (before treatment - one week after treatment). In case of significant differences in the primary outcome measure at baseline, an ANCOVA model will be used instead. If the prerequisites for t-tests are not granted, we will use non-parametric tests to compare the differences. The study will be positive if we observe a significant difference ( $p < 0.05$ ) between the intervention and the control group.

For the secondary long-term outcomes we will use Chi-squared test (for the dichotomous condition) and mixed ANOVAs with between-subject factor "group" and within-subject factor "time" for the other outcomes. Secondary short-term outcomes will be assessed using two-tailed paired t-tests.

All outcomes will be assessed in an Intention-to-Treat (ITT) analysis under the following conditions:

- The subjects who drop out before the first session will be excluded from the analysis and replaced by other subjects.
- We will continue to acquire the endpoints, keeping the same time intervals, i.e. 1, 12 and 24 weeks after the last session.
- In the case that we cannot assess the endpoint due to missing data, the subject will be excluded from the analysis and replaced by another subject.

In order to test for the robustness of the therapeutic effect, we will also conduct per-protocol analyses afterwards.

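### The post-float ECG follows tank exit and a shower, the pre-float ECG follows neither, and no rest is stated before either, so the paired HRV test counts any transient shift from those steps as a float effect

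*Combined protocol and SAP*

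**What the plan says.** The section on study procedures fixes the order at visits 2 to 6. Eligibility is rechecked and short-term outcomes 1 to 3 (acute pain, pain drawing, state anxiety) are collected, and then the first 5-minute ECG is recorded. Only then: "Subjects will then put on their bathing suits, take a shower and insert ear plugs before entering the floating tank". Next, "The float itself will take 90 minutes". For the second recording the text reads "After the floating session subjects will leave the tank and take a shower to remove excess saline. Another 5-minute ECG will be recorded"; outcomes 5 and 6 follow it.

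The study assessments section adds only the device and that HRV is measured before and after each session. The endpoints section defines improvement as a rise in high-frequency and a fall in low-frequency variability.

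For the analysis, the data analysis section says "Secondary short-term outcomes will be assessed using two-tailed paired t-tests". It names no comparison between arms for these outcomes.

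**The concern.** A before-after comparison is interpretable only if the two measurements differ in the treatment and in little else. Here the first ECG follows a period of answering questionnaires, while the second follows getting out of the tank and showering. Five-minute HRV recordings are open to short-lived influences of recent activity, and the plan states no settling time that would let them fade.

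The paired test has no term that separates such a shift from the float. A shift in the hoped-for direction would look like a benefit; a shift the other way would hide a real one. Either way, a within-arm HRV result could not be attributed to floating.

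**Working it through.** The plan states no HRV figure, so there is nothing to reproduce. The check has three parts.

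**1. The two recordings side by side** (study procedures section)

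| | First ECG | Second ECG |
|---|---|---|
| Preceding step | Short-term outcomes 1 to 3 | Leaving the tank, then a shower |
| Shower since arrival | None stated | Yes, before and after the float |
| Rest period | None stated | None stated |
| Posture | Not stated | Not stated |
| Next step | Changing, shower, ear plugs, tank | Short-term outcomes 5 and 6 |

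No other section closes the gap. The lifestyle section limits coffee and alcohol before each session but says nothing about activity or showering around the ECG.

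**2. What the planned test estimates**

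Let *f* be the effect of the session and *s* the transient shift from getting up and showering. The mean paired change in one arm estimates *f* + *s*, so *s* enters in full. The difference in change between the two floating arms estimates (*f*_I − *f*_C) + (*s*_I − *s*_C). If the shift is the same in both arms, the second bracket is zero and the shift drops out.

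**3. How much a shift could matter (illustration)**

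Assumptions: *f* = 0; one pair per patient in one arm; *s* in units of the SD of the change. Group size is 25 recruited, with a floor of 24 (sample size section). The two-sided paired t-test at 0.05 has n − 1 degrees of freedom and noncentrality *s*√n. At n = 25, √n = 5.

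| Assumed *s* (SD) | Noncentrality, n = 25 | P(significant), n = 25 | P(significant), n = 24 |
|---|---|---|---|
| 0 | 0 | 0.05 | 0.05 |
| 0.2 | 1.0 | 0.16 | 0.16 |
| 0.3 | 1.5 | 0.30 | 0.29 |
| 0.5 | 2.5 | 0.67 | 0.65 |
| 0.8 | 4.0 | 0.97 | 0.96 |

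With a common shift of any of these sizes, a test of the difference in change between the two arms would keep its 0.05 level. The converse also holds: if *s* = −*f*, the paired test rejects at only 0.05 however large the true effect.

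The number of recordings concerned is at most 2 arms × 25 patients × 5 sessions = 250 pairs. That is a count under full attendance, not a measure of bias.

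**The case against.** The strongest reply is that much of the apparent problem is silence in the text, not a stated fault. That is largely right, and it limits the point in three places.

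- **Posture and immediacy.** A reader might infer that the two ECGs are taken in different postures, or that the second starts the moment the shower ends. The documents give no posture for either recording and no interval between shower and ECG. Both could be made in the same posture after settling. What stands is that nothing requires it.
- **Warm water.** A reader might count warm water as a confounder. The shower temperature is not given, and immersion at skin temperature (35-36°C, rationale section) is part of the float itself. Only the shower, getting up and moving about are separable from it.
- **Bias between arms.** Because the later shower is there to rinse off salt, a reader might infer a longer shower after high-salinity water and hence a biased contrast with placebo. The procedure is written once for all floated patients, with no duration and no difference by arm, and the control water is described as lower in salinity, not salt-free. Such a bias cannot be excluded, but it is not shown.

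It can also be said that a within-arm paired test has a wider weakness: it absorbs 90 minutes of lying still, elapsed time and expectation as well, and matching the recordings removes none of these. This is correct. It is why the remedy needs the comparison with the control arm as well as matched recording conditions.

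Finally, HRV is one of six secondary short-term outcomes, and trial success rests on the primary pain outcome alone. That limits the weight of the point but does not remove it.

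**Conclusion.** The point holds in a limited form. Followed as written, the plan takes the two ECGs after different preceding activities, states no rest before either, and tests the change within patients. Any transient effect of getting up and showering therefore goes into the HRV result in full.

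The size and direction of that effect are unknown. The probabilities of 0.16 to 0.97 at n = 25 rest on assumed shifts of 0.2 to 0.8 SD and show sensitivity only; they are not an estimate of what happens in this trial. That a common shift cancels between arms rests on both floated arms following the same steps, as the single procedure suggests. The consequence is confined to one secondary outcome. It is a cheap improvement worth making, and not a threat to the trial's main conclusion.

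**What to change.** **In the study procedures section:** require the same posture and the same fixed rest period, for example 10 minutes, immediately before each 5-minute ECG. Record the time from tank exit to the start of the second ECG, so that departures can be seen.

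**Optional:** move the pre-float shower ahead of the first ECG. This puts a rest and a recording between the shower and tank entry, so it should be done only if it fits the requirement, in the section on floating risks, to shower before entering the tank.

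**In the data analysis section:** state that the HRV change will be interpreted by comparing it between the intervention and control arms. This removes any shift common to both and needs no extra data. It is less precise than a within-arm test: in units of the SD of the change, with 25 per arm and equal variances, the standard error is √(2/25) = 0.28 instead of 1/√25 = 0.20.

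**Cost:** two rests of 10 minutes add about 20 minutes per visit, with no new equipment. Over at most 250 visits that is 250 × 20 = 5,000 minutes, or about 83 hours of room time. The later second ECG may slightly weaken a very brief after-effect. For sessions already completed, only the change to the analysis can be made.

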## Endpoints

The study has **short-term endpoints** to assess the effect of each single floating session and **long-term endpoints** to assess the effect of a course of five successful floating sessions. While the former will be assessed before and after each floating session, the latter will be assessed one week after the final floating session and in two follow-ups at 12 and 24 weeks after completion. The only exception are pain area and widespreadness that will not be included in the follow-up assessments.

The study is successful, when the primary outcome shows significant differences between the intervention group and the control group at first assessment (one week after the final floating session).

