### Primary outcome (long-term):

The primary endpoint of the study is the reduction of pain (maximum and average) as measured by a numeric rating scale (NRS) retrospectively for one week.

**Secondary long-term outcomes** comprise improvements in

- 1.) Reduction of pain (maximum and average) by 30% or more (dichotomous)
- 2.) Pain-related disability (PDI)
- 3.) Trait Anxiety (STAI Trait)
- 4.) Depression (BDI)
- 5.) Quality of life (SF-12)
- 6.) Quality of sleep (NRS)
- 7.) Use of pain medication

**Secondary short-term outcomes** comprise improvements in

- 1.) Acute pain intensity (NRS)
- 2.) Acute pain area and widespreadness (from electronic pain drawing)
- 3.) State Anxiety (STAI State)
- 4.) Heart rate variability (improvement of sympatho-vagal balance indicated by an increase in HF- and a decrease in LF-HRV)
- 5.) Unusual bodily sensations during floating (electronic drawing)
- 6.) Altered states of consciousness during floating (5D-ASC)

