## Study assessments

- 1.) All pain scores will be acquired using numeric rating scales from 0 ("no pain") to 100 ("maximum imaginable pain"). Ratings will assess the period of one week before the day of assessment.
- 2.) Pain-related disability, state and trait anxiety, depression and quality of life will be assessed using the following validated questionnaires
  - a.) Pain disability index, PDI [9]
  - b.) State-Trait Anxiety Inventory, STAI [10]
  - c.) Beck Depression Inventory, BDI-II [1]
  - d.) 12-Item Short Form Survey, SF-12 [11]

All ratings will assess the period of one week before the day of assessment.

- 3.) Pain area and widespreadness (Widespread pain index, WPI) will be derived from electronic pain drawings acquired using the tablet PC application "SymptomMapper" developed by our group. Ratings will assess the period of four weeks before the day of assessment.
- 4.) HRV will be measured before and after each floating session using a Nilas MV Diagnostik- und Regulationssystem (Nilas MV GmbH, Hamburg).
- 5.) Unusual bodily sensations during floating will be acquired from electronic drawings with the "SymptomMapper" software.
- 6.) Altered states of consciousness will be assessed using the 5-Dimensional Altered States of Consciousness Rating Scale, 5D-ASC [4].
- 7.) Sleep quality will be assessed with a numeric rating scale. Patients will be asked how much their pain impairs their sleep on a scale from 0 ("not at all") to 100 ("very much").
- 8.) Use of pain medication will be assessed by patients' self report.
- 9.) To assess the treatment belief, subjects will receive the following written question "Which treatment do you believe you received?" and offered the replies "real floating", "placebo floating" or "uncertain".

- 10.) To assess credibility of and expectancy in the treatment, a four-item Borkovec and Nau's self-assessment scale will be used [3].

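### The visit procedure omits the post-float assessment of acute pain, pain area and state anxiety that the Endpoints section requires

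*Combined protocol and SAP*

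**What the plan says.** The outcome list, under the heading Primary outcome (long-term), numbers six secondary short-term outcomes: (1) acute pain intensity, (2) acute pain area and widespreadness, (3) state anxiety, (4) heart rate variability, (5) unusual bodily sensations in the tank and (6) altered states of consciousness in the tank.

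Endpoints sets their timing with one general rule. Of the short-term endpoints it says: "While the former will be assessed before and after each floating session".

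Study procedures on each study day gives the order of events at visits 2 to 6. On arrival, after eligibility is rechecked, "Secondary short-term outcomes 1, 2 and 3 will be assessed". A first ECG follows, then the float and a shower. The text then says: "Another 5-minute ECG will be recorded for HRV analysis (short-term outcome 4), before short-term outcomes 5 and 6 will be assessed".

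Study assessments gives explicit timing around the session for only one short-term outcome: "HRV will be measured before and after each floating session". It also sets recall periods: one week for all pain scores and for the questionnaires, among them the STAI, and four weeks for the pain drawings.

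Data analysis says: "Secondary short-term outcomes will be assessed using two-tailed paired t-tests". It does not define the pair.

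**The concern.** The visit section is the only step-by-step instruction in the document, and the contents page lists no schedule-of-assessments table that could override it. It assigns numbered outcomes to each step and says so when a measurement is to be repeated, as with the second ECG. A member of staff would reasonably conclude that outcomes 1 to 3 are taken once per visit, before the float.

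These three outcomes include both acute pain measures and make up half of the short-term list. The effect of a single session is a declared aim under Study Design and Endpoints. For pain and anxiety, that aim needs a value from each side of the float. A rating missed immediately after a session cannot be obtained later.

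**Working it through.** The plan states no figure on this point, so the check sets the sections side by side and then counts what is exposed.

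**Step 1. Tally by outcome.**

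| Short-term outcome | Before float (visit procedure) | After float (visit procedure) | Timing in Endpoints |
|---|---|---|---|
| 1 Acute pain | yes | not listed | both |
| 2 Pain area, widespreadness | yes | not listed | both |
| 3 State anxiety | yes | not listed | both |
| 4 HRV | yes | yes | both |
| 5 Bodily sensations | not listed | yes | both |
| 6 Altered states | not listed | yes | both |

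Under the visit procedure, the outcomes measured on both sides are {4}, those measured only before are {1, 2, 3}, and those measured only after are {5, 6}.

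**Step 2. Pairs per patient.** Visits 2 to 6 are five sessions. For each of outcomes 1 to 3, the visit procedure alone yields 0 within-session pairs out of 5. The rule in Endpoints yields 5 out of 5.

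**Step 3. Other possible pairs.** Because Data analysis leaves the pair undefined, a paired test could still be run on pre-float values from successive visits. Those visits are 4 ± 2 days apart, so the difference would mix the session effect with whatever happened in between. It would not answer the single-session question that Endpoints poses.

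**Step 4. Worst-case count.** The inputs are two float arms (Study Design; the waiting-list arm has no sessions), 24 to 25 patients per arm (Study population / Sample size calculation), five sessions and three outcomes.

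- Sessions: 2 × 24 × 5 = 240, up to 2 × 25 × 5 = 250.
- Post-float assessments: 240 × 3 = 720, up to 250 × 3 = 750.

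This assumes that every patient attends all five sessions and that staff follow the visit procedure to the letter.

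**Step 5. Would a second rating measure an acute change?** Read literally, the recall rules in Study assessments cover outcomes 1 to 3: one week for pain scores and the STAI, four weeks for the drawings. A float lasts 90 minutes. Two ratings about 90 minutes apart, each looking back one or four weeks, refer to almost the same period. Adding the post-float ratings without changing the recall period would therefore give pairs that do not capture the session effect.

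**Step 6. Outcomes 5 and 6.** Both describe experiences in the tank, so collecting them only afterwards is natural. The general timing rule in Endpoints and the general paired test in Data analysis do not fit them.

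**The case against.** A reader might infer that the protocol never plans post-float values for pain and anxiety, so that the before-after comparison is impossible by design. The documents do not support that. Endpoints commits to assessment on both sides of the session, and Study Design also speaks of endpoints evaluated after each one. The intended design is therefore stated, and one procedural paragraph fails to carry it through. That part of the objection stands: this is an internal inconsistency, and the data may well be collected.

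For the same reason, the 720 to 750 assessments cannot be read as an established loss. The forms used at the visits are not in the document, and a form that prompts for the second rating would prevent the loss.

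The paired test in Data analysis is weaker support than it looks, because its pair is undefined. The before-after requirement comes from Endpoints.

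The affected outcomes are also secondary. The primary outcome, the success criterion and the sample size all rest on retrospective pain and do not depend on any rating made at a float visit.

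The objection does not remove the problem. The rule in Endpoints is general and does not suit outcomes 5 and 6, so staff must turn to the visit procedure to learn what to collect and when. That text omits the ratings, and the introductory note says the approved protocol was not altered afterwards.

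**Conclusion.** The contradiction between Study procedures on each study day and Endpoints is real and should be reconciled before the first float visit. If the visit procedure is followed literally, no within-session comparison is possible for acute pain, pain area and widespreadness, or state anxiety. At full attendance that puts 240 to 250 sessions and up to 720 to 750 post-float assessments at risk. How many would in fact be missing cannot be determined from the document.

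The damage is confined to three secondary short-term outcomes. The trial's main conclusion is not threatened. The point still merits correction, because the loss would be systematic and irrecoverable and the repair is small.

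**What to change.** Four sections need a short edit:

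- **Study procedures on each study day:** state that short-term outcomes 1, 2, 3, 5 and 6 are assessed after the post-float ECG. Any visit form should match.
- **Study assessments:** exempt outcomes 1 to 3 from the one-week and four-week recall periods when they are taken at float visits, and state that they refer to the current moment.
- **Endpoints:** state that outcomes 5 and 6 are collected only after the float.
- **Data analysis:** define the pair for outcomes 1 to 4 as the values before and after the same session. State that outcomes 5 and 6 are not analysed as before-after pairs, and name the comparison to be used for them.

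The cost is a few extra minutes of questionnaires per session and an amendment, which the Amendments section requires to be presented to the ethics committee. If visits have already taken place, check the completed forms and report how many sessions have both values.

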## **Dietary/Lifestyle restrictions and concomitant medication**

Subjects must not drink coffee for 6 hours and alcohol for 24 hours before each floating session.

Subjects should not shave any part of their body for 6 hours before each floating session.

The use of prescribed medications for the pain condition as well as acute medications that do not interfere with the study, as judged by the investigator, is permitted during the study, if necessary.

Subjects must continue their prescribed medication during the intervention and must not start any new therapeutic intervention (pharmacological or other).

The administration of acute and prescribed medication will be documented giving the name of the drug, the applied dosage, the time-point, and the reason.

## **Data handling**

All source data will be saved pseudonymously. There will be a reference list, which will be kept separated from the study data. All responsible persons are bound to maintain confidentiality. Source data will be kept for at least ten years. Subjects are entitled to ask for the immediate deletion of their data without any prejudices.

